### 2.3. Randomisation and Blinding

The selected sample (*N* = 210) will be randomly divided into two groups: one group will receive treatment through a telerehabilitation programme based on the exercise protocols of the McKenzie method combined with analgesic electrotherapy, while the control group will follow the same face-to-face programme. This allocation will be performed in an equitable and blinded manner using a list of random numbers generated by Epidat 4.2 software. These cards with individual numbers will be folded and placed in opaque envelopes so that a blinded member of the study can subsequently open the envelope and assign the subject to one of the intervention groups. Each group (telerehabilitation and control) will be divided into three subgroups according to the McKenzie classification: postural, dysfunction, and derangement. The evaluator and the statistician of the study will remain blinded throughout the entire study. The assessor will not attempt to identify the participants’ group assignments, and the data provided to the statistician will be anonymised to ensure confidentiality and unbiased analysis. To ensure anonymisation, any identifiable personal information will be deleted, and a unique ID will be assigned by the principal investigator to each participant before the data are sent to the statistician. The file containing the non-encrypted information will be kept by the principal researcher. Due to the nature of the interventions, neither the participants nor the principal researcher responsible for the treatment will be blinded.

The telerehabilitation programme will use a support system for the treatment of cervical pain based on web technologies, accredited as a healthcare website. This system has a structure based on four sections: database management, database user profiles, recommendations, and feedback/biofeedback procedures. This system allows for registering and entering a subject and modifying a treatment with electroanalgesia and exercises, according to the symptomatic evolution of the pain. It is based on an initial patient assessment system. Once the initial diagnosis of the patient is made according to the McKenzie clinical subtypes of NP, a multimedia database will be developed with examples of specific treatments (according to symptom evolution) for postural syndrome, dysfunction syndrome, and derangement syndrome. Patients will use their computer or mobile device connected to the internet to access the platform, where they will find the videos of the combined application of electroanalgesia and exercises. The treatments will be provided by the system. The database is configured to accommodate the application of electroanalgesia and exercises based on the diagnosis according to the McKenzie method. Each subgroup corresponds to a programme and a set of previously defined exercises with electroanalgesia as well as recommendations for daily activities, such as manual activity, sitting, standing, or ergonomic postures for daily activities. Therefore, each treatment will use a feature vector VT with 3 characteristics (one for each subgroup), where each position will contain a value indicating the degree of difficulty for each treatment subgroup. The system calculates and recalculates recommendations and updates the values of the relevance estimates for the recommended treatments. The system will recommend treatment Y for subject X, and depending on the modification or remission of the pain, at the start of each session, it will continue with the same plan or will be adjusted following the therapeutic algorithm of the McKenzie method. Once the treatment is completed, the outcome measures will be evaluated. This evaluation will be recorded in the system to be subsequently available in the recommendation processes. Furthermore, the system recalculates the evaluations provided by the patients. To facilitate the correct execution of the treatment, each element on the website is arranged in the order in which it should be performed and represented by icons that are easily associated with each step. This ensures that patients are guided intuitively as they scroll through the website. To verify attendance and ensure that patients complete all sessions properly, patients must enter their ID in the field provided on the website at the end of each session. This confirmation will be emailed automatically to the responsible clinician.

Patients in the face-to-face programme will receive the same treatment as described above, delivered face-to-face by six therapists, each with over 10 years of experience in both intervention procedures. This programme will be developed at the rehabilitation and physiotherapy services of the Andalusian Health Service (Almería, Granada and Málaga), Spain.

### 2.5. Data Collection

Measurements will be taken at three timepoints: before the start of treatment (baseline), after completing the eight-week intervention (post-treatment), and six months after the final session (follow-up). Patients from both groups will be scheduled to attend in person to complete the questionnaires at each assessment; demographic and clinical data, healthcare resource utilisation, associated costs, and sick leave will be recorded.

### 2.6. Outcomes

The main outcome measure will be the healthcare resources used during the study, and their costs will be collected through questionnaires completed by the participants at baseline, post-treatment, and follow-up (6 months). Table 1 provides a detailed list of the relevant resource categories, the sources from which usage data are obtained, and the associated unit costs, Table 2 shows timepoints of assessments. The cost analysis will include resources and expenses related to primary and hospital care, diagnostic testing, and other direct out-of-pocket expenses incurred by the participants (e.g., transportation costs). In addition, the social costs associated with absenteeism and loss of productivity will be included as secondary outcomes. For each participant, information on their resource utilisation will be tracked by means of a receipt log. At each assessment, patients will be asked to recall and detail their use of the described resources during the preceding months. These data will then be converted into costs based on updated unit prices from official sources.

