## Abstract

**Background/Objectives**: Neck pain is a complex biopsychosocial condition that affects a significant proportion of the global population. Projections indicate that over the next 30 years, cervical pain will impact approximately 269 million individuals, positioning it as one of the primary drivers of healthcare expenditure and system burden worldwide. While exercise is a key approach for neck pain, the effectiveness and cost-effectiveness of treatments delivered remotely remain underexplored. The aim of this study is to analyse the cost-effectiveness and cost-utility of the treatment of non-specific neck pain through a telerehabilitation programme based on cervical exercise and analgesic electrotherapy. **Methods**: This is a study protocol for an economic evaluation based on a randomised controlled trial (RCT) with a sample size of 210 participants (*N* = 210). The sample will be evenly divided into two groups to perform the same cervical exercise programme combined with electroanalgesia: one group will receive the intervention via telerehabilitation, and the other will receive the intervention face-to-face. Three sessions will be held per week for eight weeks for a total of 24 sessions. Demographic and clinical data of the participants, healthcare resource utilisation, and associated costs will be collected. Assessments will be carried out throughout the study: before the first session (baseline), at 8 weeks (post-intervention), and 6 months after completion of the treatment (follow-up). **Discussion**: This study will make a significant contribution to reducing costs and improving the treatment of patients with non-specific chronic neck pain. The social perspective associated with economic evaluation will enable the investigation of indirect costs such as work absenteeism or expenses borne by the patient, providing useful data to optimise planning and decision-making in the healthcare sector.

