NP is linked to impaired work performance and imposes a considerable economic burden on both individuals and healthcare systems. In the United States, it is estimated that there are approximately 10.2 million annual visits to physiotherapists or hospitals due to NP [1]. In Belgium, Gorasso et al. estimated the direct annual cost per patient at EUR 2212—36% higher than for individuals without NP [9]. Meanwhile, the Netherlands reported total costs of USD 686 million for related conditions [10]. Economic evaluations in healthcare distinguish between direct costs (related to the use of services and resources) and indirect costs (related to lost productivity, quality of life, and reduced independence). Indirect costs often exceed direct medical and pharmaceutical expenses [11]. The majority of health-related expenditure is caused by so-called presenteeism, which refers to reduced productivity due to attending work while ill and performing below usual standards, and is simultaneously the greatest risk factor for experiencing periods of sickness absence [12]. Economic losses resulting from presenteeism due to NP constitute a global problem affecting the world’s leading economies, with annual per capita losses of USD 1290 in the USA (an approximate total of USD 11.87 billion) and USD 414.05 per capita in Japan (an approximate total of USD 28 billion) [12,13]. A key factor in reducing the costs of NP treatment appears to be early intervention, as a delayed start to treatment may result in an increase in total costs of up to 117% [14]. To truly understand the economic impact of a disease, two main types of analysis can be used: cost-effectiveness and cost-utility. In the field of health economic evaluation, cost-effectiveness analysis allows decision-making and comparison of interventions by considering both the costs of a treatment and how effective that treatment is for at least two competing strategies [15], while cost-utility analysis also incorporates quality of life [16].

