### 2.7. Sample Size and Data Analysis

The sample is calculated with the sample size calculation of Willan [40]. Like many of the parameters that were used, these were unknown, and assumptions were made about health parameters as the difference between the average cost of both treatments was assumed in monetary terms from EUR 300, and the standard deviation of the monetary costs was EUR 600. In addition, the effect of the intervention and the difference between means, to be detected in NDI, is 7 units, having a common variance in NDI in patients with neck pain of 10, which is a clear overestimation of the standard deviation. The correlation coefficient between effectiveness and cost is 0.1, clearly underestimated so that the sample size is increased, with an alpha error of 0.05 and a power of 80%. With these conditions, the sample size was 105 patients with neck pain per group (telerehabilitation programme group and face-to-face programme group). In each group, these patients will be divided into three subgroups (postural, dysfunction, and derangements syndromes).

We will register the number of days that patients are on sick leave due to neck pain, family cost, primary and secondary healthcare consultations (Andalusian Health Service provider), diagnostic test (Andalusian Health Service provider), additional medical services (Andalusian Health Service provider), material provided in intervention (production cost), and direct non-healthcare cost (aid to patients who face disabilities), and work absenteeism cost will be measured using days of work sick leave by salary.

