### 2.8. Economic Evaluation

An economic analysis will be performed in STATA 19, including a CEA and a CUA, with the aim of estimating and comparing the incremental costs and benefits of the telerehabilitation and face-to-face care programmes. A six-month time horizon was chosen to capture not only the immediate effects of the interventions but also the costs and outcomes that arise during the months following their implementation. This duration allows a more comprehensive assessment of the interventions’ impact from a societal perspective. Missing cost data will be handled using appropriate techniques, such as multiple imputation, according to the type and magnitude of the missing data. We will use multiple imputation by chained equations. The imputation model will include all variables used in the CEA and CUA, assuming that data are missing at random. We will generate 20 imputed datasets, each analysed separately using the same statistical procedures. The results will then be pooled according to Rubin’s rules, providing unbiased estimates of variances that account for the uncertainty associated with imputed values. Given that the cost distribution is usually skewed due to the presence of patients with very high costs, the mean cost per patient will be presented together with confidence intervals obtained using non-parametric bootstrap methods [41]. QALYs will be calculated as the area under the curve connecting the utility scores recorded at baseline and at subsequent follow-up points. The results will be expressed as incremental cost-effectiveness ratios (ICERs), which reflect the additional cost per each additional unit of outcome achieved. An incremental analysis will be performed to calculate the difference in costs and the difference in outcomes (improvements in effectiveness measured in QALYs) associated with the telerehabilitation and face-to-face programmes. In order to address the uncertainty associated with sample variability, the joint distribution of the differences in costs and effects will be estimated through multiple simulations using non-parametric bootstrap methods. The simulated cost-effectiveness pairs will be graphically represented on a cost-effectiveness plane, and acceptability curves will be generated to reflect the probability that each alternative is cost-effective according to different willingness-to-pay thresholds per QALY [42]. In Spain, the value of a QALY is estimated to be between EUR 22,000 and EUR 25,000 [43]. A sensitivity analysis will be carried out to assess the robustness of the results against different values, assumptions, and methodological approaches [44]. As the time frame of this study is limited, it will not be necessary to apply discounting to costs or benefits. The economic analysis will be reported in accordance with the guidelines of the Consolidated Health Economic Evaluation Reporting Standards (CHEERS) [45].

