## Figures and Tables

**Table 1 healthcare-13-03076-t001:** Cost measures.

Costs	Breakdown	Source of Cost/Unit	Cost Calculation
Direct Medical Costs			
Primary care	General medicine	Andalusian Health Service	No. of visits × rate per visit
	Nursing		
	Physiotherapy		
Emergency hospital visits	General medicine	Andalusian Health Service	No. of visits × value per visit
	Nursing		
Referrals to services	Traumatology, Rehabilitation, etc.	Andalusian Health Service	Specialty × fee per visit
Home assistance	Ambulance	Andalusian Health Service	Service × fee-for-service
	General medicine		
	Nursing		
Diagnostic tests	X-rays, MRI, CAT Scans, etc.	Andalusian Health Service	Test × test price
Medicines	Muscle relaxants, analgesics, NSAIDs, etc.	Standard drug prices according to the Official General Council of Pharmacists	Medicine × price of the medicine
Non-medical direct costs			
Patient’s transport expenses	Bus	Patient	Number of times × price each time
	Taxi		
	Own transport (petrol)		
Indirect costs			
Absenteeism	Sick leave days	Patient and according to the assigned professional classification (National Statistics Institute of Spain)	Days of sick leave × daily wage

Magnetic resonance imaging (MRI), computed axial tomography (CAT), non-steroidal anti-inflammatory drugs (NSAIDs).

**Table 2 healthcare-13-03076-t002:** Timepoints of assessments.

Timepoint	Study Moment										
	Enrolment	Treatment								Follow-up	
	0W	1W	2W	3W	4W	5W	6W	7W	8W	2M	6M
	July 2025	July–September 2025								September 2025	January 2026
Screening and enrolment											
Eligibility screening	X										
Informed consent	X										
Allocation	X										
McKenzie classification	X										
Interventions											
Telerehabilitation programme (experimental)		3 Times per week									
Face-to-face programme (control)		3 Times per week									
Assessments											
Demographic variables		X									
Economic evaluation		X								X	X

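### The plan promises loss-of-productivity costs from a societal perspective but costs productivity only as sick-leave days, omitting presenteeism and working time lost to 24 clinic visits

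*Protocol article*

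**What the plan says.** Section 2.6 makes healthcare resource use and its cost the main outcome and adds that "the social costs associated with absenteeism and loss of productivity will be included as secondary outcomes". Section 2.8 justifies the time horizon thus: "This duration allows a more comprehensive assessment of the interventions’ impact from a societal perspective". The Abstract is narrower: "The social perspective associated with economic evaluation will enable the investigation of indirect costs such as work absenteeism or expenses borne by the patient".

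Three places say how lost work is measured, and they agree:
- Section 2.5, on what is collected at each assessment: "demographic and clinical data, healthcare resource utilisation, associated costs, and sick leave will be recorded".
- Section 2.7: "work absenteeism cost will be measured using days of work sick leave by salary".
- Table 1, in its single indirect-cost row: "Days of sick leave × daily wage".

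The Introduction treats reduced output while at work as distinct from sickness absence and says of it: "The majority of health-related expenditure is caused by so-called presenteeism". The Conclusions list treatment without interruption of work among the possible advantages of telerehabilitation.

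**The concern.** The stated scope is wider than the measurement. Two kinds of lost productivity fall outside a count of sick-leave days. One is reduced output while at work, which the article itself ranks first. The other is time away from work for treatment: an hour taken off for an appointment is not a day of sick leave.

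The second kind is not spread evenly. Control patients attend 24 sessions at health-service sites, while telerehabilitation patients follow the same programme through a website. Table 1 costs the fare for a journey but not the time. A cost that one arm bears by design, and that is left out, shifts the between-arm cost difference whatever the sample size. The trial would also have no data on the work-related advantage that its Conclusions put forward.

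**Working it through.** **Scope against measurement.** Section 2.6 names absenteeism and loss of productivity. Sections 2.5 and 2.7 and Table 1 supply one work item, sick leave. Section 2.6 introduces Table 1 as the detailed account of resource categories, data sources and unit costs, so the costing rule for lost work is stated rather than merely deferred. The article shows no questionnaire, item or valuation for presenteeism or for hours lost to treatment.

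**The plan's own figure.** The article gives no estimate of productivity cost to reproduce. The yardstick is the cost difference of EUR 300 assumed in section 2.7.

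**Clinic time.** Inputs: 24 sessions (section 2.4). Assumed, because the article gives no value: 1 to 2 hours per visit and EUR 10 to 20 per hour.

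Gross cost per affected control patient = visits × hours per visit × hourly wage
- Low: 24 × 1 × 10 = EUR 240
- High: 24 × 2 × 20 = EUR 960

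This is an upper bound on the between-arm gap, for two reasons.
1. Not everyone loses paid time. Eligibility is age 30 to 65, with no employment requirement. If an assumed 60% are affected, the gross arm mean is 0.6 × 240 = EUR 144 to 0.6 × 960 = EUR 576.
2. Telerehabilitation patients also spend time on 24 sessions. Only the extra time in the control arm counts: mainly travel, waiting and fixed appointment hours. Each net extra hour per visit adds 24 × 0.6 × 10 = EUR 144 to 24 × 0.6 × 20 = EUR 288 to the arm mean, which is 48% to 96% of EUR 300. The gap would equal EUR 300 at 300 / 288 = 1.04 net hours per visit at the higher wage, or 300 / 144 = 2.08 at the lower.

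**Direction.** The omitted time belongs to the face-to-face arm. Leaving it out makes face-to-face care look cheaper than it is, so the societal comparison is biased against telerehabilitation.

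**Presenteeism.** Inputs: annual per-capita losses of USD 1290 (USA) and USD 414.05 (Japan), from the Introduction. Period: 8 weeks of treatment plus 26 weeks of follow-up = 34 weeks.
- 1290 × 34/52 = USD 843
- 414.05 × 34/52 = USD 271

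An assumed 20% difference between arms is 0.2 × 271 = USD 54 to 0.2 × 843 = USD 169. Over six months alone (the horizon named in section 2.8) the losses are USD 207 to 645, and 20% of that is USD 41 to 129. These amounts are in US dollars and are not converted. The 20% has no source in the article. Both arms receive the same programme, so the true difference could be close to zero, and its sign is unknown.

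**The case against.** The best defence has four parts.

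**The stated perspective may be narrower than it sounds.** The Abstract's examples of indirect cost are work absenteeism and patient expenses, both of which Table 1 covers. On that reading, loss of productivity in section 2.6 simply means output lost through absence. This is possible, but section 2.6 names the two side by side, and the Introduction separates reduced output at work from sickness absence. At the least, the term is undefined.

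**Table 1 is not complete.** Section 2.7 also lists family cost, intervention material and aid for disability, none of which has its own row in Table 1. It would therefore be wrong to say that the plan reduces to healthcare, transport and sick leave. Family cost is undefined and might hold some time cost, but nothing says that it covers working hours. A fuller protocol may contain further items, so the accurate statement is that no such item is shown.

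**The article does not give two competing totals.** A reader might infer this from the societal wording in section 2.8 beside the healthcare outcome in section 2.6. Section 2.6 in fact ranks them: healthcare cost is the main outcome and social costs are secondary. That is a legitimate hierarchy, and putting the societal total first would be a preference. What remains is that section 2.8 does not say which total enters each ICER.

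**The amounts are assumed.** The full EUR 240 to 960 should not be read as the bias: it is gross and applies only to patients who lose paid time at every visit. This stands, and it limits the finding to a range.

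**Conclusion.** The point holds as a mismatch between claimed scope and defined measurement, and it should be corrected. The mismatch itself needs no assumption; its size does. The clinic-time omission runs in a known direction, provided that control patients lose more working time than telerehabilitation patients. On the assumptions shown, it is EUR 144 to 288 in the arm mean for each net extra hour per visit, against a planned EUR 300. The presenteeism omission is of unknown direction and could be negligible.

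A reader might go further and infer that the societal conclusion could change sign. The documents do not show that. The clinic-time bias works against telerehabilitation, so a societal result in its favour would be conservative on that item. The main healthcare-cost outcome is not affected.

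**What to change.** 1. Add to the existing questionnaires, in both arms, the working hours lost per treatment session, and a brief presenteeism item (days worked with neck pain and percentage of usual output). Ask patients not to count the same hours again as sick leave.
2. Add matching rows to Table 1, each with its source and valuation.
3. Report the societal result with and without presenteeism.
4. Keep the outcome hierarchy of section 2.6, and state in section 2.8 which cost total enters each ICER.

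Trial Status gives 1 July 2025 as the start of recruitment, and section 3 says that outcomes are fixed once the first participant is registered, while also providing for changes to be communicated and disclosed. If baseline has passed, collect hours lost by recall at the remaining visits and report this as an amendment by that route. If new items cannot be added, name the perspective by what is measured (healthcare, patient out-of-pocket and transport costs, and sick-leave absenteeism), and drop both the reference to loss of productivity and the remark about uninterrupted work.

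The cost is a few questions at visits already planned, a slight added burden on participants, and more variable cost data. Renaming the perspective costs only a change of wording.
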